# The effects of different forms of daily exercise on metabolic function following short-term overfeeding and reduced physical activity in healthy young men: study protocol for a randomised controlled trial

**DOI:** 10.1186/s13063-018-2579-6

**Published:** 2018-03-27

**Keywords:** Exercise, Overfeeding, Reduced physical activity, Arm crank, Breaking sitting, Moderate-intensity exercise, Metabolism, Adipose tissue, Skeletal muscle and energy imbalance

## Abstract

**Background:**

Short-term overfeeding combined with reduced physical activity impairs metabolic function and alters the expression of key genes within adipose tissue. We have shown that daily vigorous-intensity running can prevent these changes independent of any net effect on energy imbalance. However, which type, intensity and/or duration of exercise best achieves these benefits remains to be ascertained.

**Methods/design:**

Forty-eight healthy young men will be recruited and randomly allocated to one of four experimental conditions for 1 week: (1) to ingest 50% more energy than normal by over-consuming their habitual diet whilst simultaneously restricting their physical activity below 4000 steps day^−1^ (i.e. energy surplus; SUR group); (2) the same regimen but with a daily 45-min bout of vigorous-intensity arm crank ergometry at 70% of maximum oxygen uptake (SUR + ARM group); (3) the same regimen but with a daily 45-min bout of moderate-intensity treadmill walking at 50% of maximum oxygen uptake (SUR + MOD group); (4) the same regimen but with the addition of intermittent short bouts of walking during waking hours (SUR + BREAKS group). Critically, all exercise groups will receive additional dietary energy intake to account for the energy expended by exercise, thus maintaining a matched energy surplus. At baseline and follow-up, fasted blood samples, abdominal subcutaneous adipose tissue and skeletal muscle biopsies will be obtained and oral glucose tolerance tests conducted.

**Discussion:**

This study will establish the impact of different forms of daily exercise on metabolic function at the whole-body level as well as within adipose tissue and skeletal muscle in the context of a standardised energy surplus.

**Trial registration:**

ISRCTN, ISRCTN18311163. Registered on 24 June 2015.

**Electronic supplementary material:**

The online version of this article (10.1186/s13063-018-2579-6) contains supplementary material, which is available to authorized users.

## Background

It is generally accepted that regular physical activity/exercise is an important part of a healthy lifestyle and that physical inactivity increases the risk of disease over the long term [1]. Both an acute bout of exercise and chronic endurance training can have beneficial effects on outcomes that are important for health, such as insulin action. Earlier work by Hagobian and Braun [2] reported rapid metabolic dysregulation following 3 days of overfeeding without structured exercise in a cohort of habitually active participants. Importantly, however, a single bout of moderate-intensity exercise restored insulin responses to baseline despite additional overfeeding on the final day to match energy expended during exercise. This finding presents the interesting possibility that exercise has the potential to impact metabolism independent of any effect on energy balance. In order to understand and isolate how exercise exerts its effects on metabolism, it is critically important to conduct studies where energy status is carefully controlled [3]. Human models where physical activity/exercise and energy balance are manipulated offer an opportunity to tease apart the impact of exercise above and beyond its impact on energy balance and/or adiposity. One of the most powerful ways to examine this question is through a deliberate attempt to create an energy surplus with and without various forms of physical activity.

Various studies have investigated the impact of reduced physical activity on health outcomes in healthy, active individuals. Both short-term and longer-term physical inactivity, induced by restricting structured exercise [4, 5] or by reducing the daily number of steps [6, 7], have consistently led to a decrease in insulin sensitivity. More extreme bed-rest studies have also shown how complete physical inactivity can reduce insulin sensitivity and alter the skeletal muscle transcriptome [8–11]. Numerous studies have investigated the impact of positive energy balance induced through overfeeding of varied duration and composition on metabolic outcomes. Excessive energy intake impairs insulin sensitivity [12–14] and alters adipose gene expression [15–17]. Many metabolic diseases such as type 2 diabetes, obesity and the metabolic syndrome result from a chronic state of energy imbalance created by low physical activity and/or an excessive energy intake. It is remarkable that very few studies have used experimental models to investigate the joint impact of both factors applied concurrently.

The combination of overfeeding and decreased physical activity can impair glycaemic control and insulin sensitivity [18–20]. Our previous work has shown that short-term overfeeding combined with reduced physical activity induces a state of insulin resistance, hyperinsulinaemia and altered expression of key genes within adipose tissue [20]. The addition of daily *vigorous-intensity running* mostly prevented these changes independent of any net effect on energy imbalance. Whilst running involves a large muscle mass and has the potential to expend many calories (potentially providing a route of disposal for excess glucose), it is unknown whether other forms of physical activity have the same impact. Alternative forms of exercise may be more appropriate for or preferred by specific populations.

The objectives of the proposed study are to evaluate three alternative but energy-matched physical activity/exercise models:To establish whether a daily bout of *vigorous-intensity upper-body exercise* can prevent negative changes in metabolic function induced by short-term overfeeding and reduced physical activityTo establish whether a daily bout of *moderate-intensity treadmill walking* can prevent negative changes in metabolic function induced by short-term overfeeding and reduced physical activityTo establish whether *several short bouts of walking* throughout the day can prevent negative changes in metabolic function induced by short-term overfeeding and reduced physical activity

## Methods/design

### Participants

To address these objectives, a cohort of 48 healthy young men who satisfy the inclusion and exclusion criteria outlined below will be recruited via advertisement from the local community. Written consent will be obtained from all participants after the initial meeting, and participants will be informed that they can withdraw from the study at any time without consequence. Eligibility will be assessed by a series of self-report questionnaires. Eligible participants will then be randomly allocated to one of four parallel intervention arms using a stratified randomisation scheme. The randomisation schedule will be generated by a senior author ([name]) using an electronic random number generator and concealed from those involved in participant management ([name]) to prevent biased allocation [21, 22]. Participant assignment will be requested via email, and full details of the overall randomisation scheme will be published once all allocations are completed to prevent deciphering. This will feature a factor for objectively measured physical activity level (PAL) and body mass to ensure an even distribution of less active (PAL: <1.75) and more active (PAL: ≥1.75) as well as lighter (<77 kg) and heavier (≥77 kg) participants in each treatment arm, respectively. The ensuing protocol for this study has received ethical approval from the National Health Service Research Ethics Committee (reference: 15/SW/0014).

Inclusion:Male.Aged 18–40 years old.Active (exercise more than 30 min per day, at least three times per week).Stable body mass for at least 6 months (<3% increase or decrease [23]).Able and willing to comply with study procedures.Have the capacity to provide informed consent.

Exclusion:Female.Currently smoking.Aged less than 18 years or greater than 40 years.Positive response to one or several questions from the Physical Activity Readiness Questionnaire (PAR-Q).Taking any medication that might interfere with the study outcomes (This will be reviewed by the research team on a case-by-case basis should a potential participant be on regular medication. The British National Formulary will be checked for potential effects that might introduce bias in the study.).Illness/condition that might interact with study measures (e.g. diabetes, heart disease) or pose undue personal risk.

### Power calculation

We plan to recruit 48 young (18–40 years), healthy, weight-stable, active men from the local population. Using data from our previous study [20], it was estimated that a sample size of 12 in each treatment group will provide approximately 90% power to detect a difference in ∆ insulin iAUC of 17 ± 16 versus 1 ± 6 nmol 120 min L^−1^ using an independent *t* test at an alpha level of 0.05. Recruitment will proceed on a rolling basis until the adequate sample size is reached; emphasis will be placed on considering the demands of the study before enrolling to reduce loss to follow-up.

### Statistical analysis

All data from participants having successfully completed the study will be included in the analysis. The statistical analysis plan is for a primary comparison between intervention groups and control arm. The precise time-course of responses within and between trials will be analysed using factorial two- and three-way mixed-model analysis of variance (group × day and group × day × time, respectively). For all the above statistical approaches, statistical significance will be set at an alpha level of *p* ≤ 0.05. We will explore the use of confidence intervals and magnitude-based inferences to assess the clinical significance of the effect.

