### Main trial day protocol

The same experimental procedures will be completed on both baseline and follow-up trial days. During 3 days leading up to the intervention week, volunteers will be asked to adhere to their habitual lifestyle (i.e. diet and physical activity/exercise), and all participants will be asked to perform a 30-min bout of running the day before starting the intervention before 1400 h at their usual running pace. This will ensure that the last bout of exercise will have been standardised for all participants. On the morning of the baseline trial (Fig. 2), participants will report to the laboratory at 0700 ± 0.5 h following an overnight fast (≥10 h). Twenty-four hours prior to each main laboratory trial day, participants will abstain from caffeine (tea/coffee) and alcohol. The SPIRIT figure showing the respective time points for assessments and intervention is provided in Fig. 3 (see Additional file 1).

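### With two trial days, the named group × day ANOVA amounts to an unadjusted change-score comparison that uses neither baseline as a covariate nor the stratification factors: valid, but possibly less efficient

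*Protocol article*

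**What the plan says.** The Statistical analysis section first sets the main contrast: "The statistical analysis plan is for a primary comparison between intervention groups and control arm". No model is attached to that sentence. The only models named come in the sentence after it, and they are "factorial two- and three-way mixed-model analysis of variance (group × day and group × day × time, respectively"). The stated purpose of those models is the time course, since that sentence opens: "The precise time-course of responses within and between trials will be analysed using". No covariate is mentioned in either sentence.

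Three other places bear on it:

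- **Main trial day protocol:** "The same experimental procedures will be completed on both baseline and follow-up trial days". The day factor therefore has two levels.
- **Power calculation:** the trial is sized on a "difference in ∆ insulin iAUC of 17 ± 16 versus 1 ± 6 nmol 120 min L^−1", with an independent t test, 12 per group, alpha 0.05 and about 90% power. That is also an unadjusted change score.
- **Participants:** men are "randomly allocated to one of four parallel intervention arms using a stratified randomisation scheme". On the scheme, the article says: "This will feature a factor for objectively measured physical activity level (PAL) and body mass to ensure an even distribution". The cut-points are a PAL of 1.75 and a body mass of 77 kg. Neither factor appears in the analysis section.

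**The concern.** A group × day interaction with one baseline and one follow-up day fixes the coefficient of baseline at 1. Baseline-adjusted analysis estimates that coefficient instead. For a two-arm comparison with equal allocation, adjustment is in large samples never less precise than the change score, and it is more precise unless the true slope is 1.

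The strata raise a related point. Stratified allocation balances PAL and body mass across arms. If they predict the change in insulin iAUC and are left out of the model, their variation stays in the residual, and the standard errors are larger than the design warrants.

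With 12 men per arm, even a modest efficiency gain would be worth having, and every variable needed is already measured before the intervention.

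**Working it through.** **Inputs.** From the Power calculation section: mean changes 17 and 1, SDs 16 and 6, 12 per group, alpha 0.05 (two-sided assumed, as sidedness is not stated). From Main trial day protocol: two days. Assumed, because the document does not give them: the baseline–follow-up correlation ρ, the baseline and follow-up SDs, and the share of variance explained by the strata.

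**1. The plan's own figure.** Mean variance = (16² + 6²)/2 = 146, so SD = 12.08. Difference = 17 − 1 = 16; standardised, 16/12.08 = 1.324. Noncentrality = 1.324 × √(12/2) = 3.244.

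- Normal approximation, two-sided: power 0.900. This reproduces the stated 90%.
- Noncentral t with 22 df, the test the article names: 0.873.
- Welch version for unequal variances (about 14 df): 0.854.

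The comparator below is 0.873.

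**2. Equivalence.** On simulated data with four arms of 12 and two days, the group × day F and the one-way F on change scores are both 3.469. The three-way term is different: it compares change profiles across the OGTT and is not a single change score, though it too has no covariates.

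**3. Baseline adjustment, equal variances on both days.** Variance ratio, ANCOVA to change score = (1 − ρ²)/[2(1 − ρ)] = (1 + ρ)/2. Estimating the slope from 24 men multiplies the variance by about 1 + 1/(2 × 12 − 4) = 1.05 and leaves 21 df.

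| Assumed ρ | (1 + ρ)/2 | Power (change score 0.873) |
|---|---|---|
| 0.3 | 0.65 | 0.963 |
| 0.5 | 0.75 | 0.936 |
| 0.7 | 0.85 | 0.905 |
| 0.8 | 0.90 | 0.889 |
| 0.9 | 0.95 | 0.872 |

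**4. Unequal variances on the two days.** With baseline SD s₁ and follow-up SD s₂, the ratio is s₂²(1 − ρ²)/(s₁² + s₂² − 2ρs₁s₂). It reaches 1 when the baseline slope ρs₂/s₁ equals 1.

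- s₂/s₁ = 1.2, ρ = 0.5: ratio 0.871, power 0.899.
- s₂/s₁ = 1.5, ρ = 0.7 (slope 1.05): ratio 0.998, power 0.856.
- Slope exactly 1: power 0.855, a loss of about 2 points.

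**5. Holding the plan's change SDs at 16 and 6.** Let b be a common baseline slope. Change variance in each arm is (1 − b)²s₁² plus residual variance, so (1 − b)²s₁² cannot exceed 6² = 36. Mean residual variance is then at least 146 − 36 = 110, and the ratio at least 110/146 = 0.753. Simulations with assumed baseline SDs of 10 to 15 gave, for change score versus ANCOVA:

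- slope 1: 0.867–0.873 versus 0.849–0.856;
- slope 0.8: 0.868–0.870 versus 0.864–0.874;
- slope 0.6–0.7: 0.869–0.876 versus 0.890–0.896.

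**6. Adding the two strata, at ρ = 0.7 and equal variances.** With balanced strata and 19 df, power is 0.902 if they explain nothing, and 0.929 if they explain an assumed 10% of the residual variance.

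**The case against.** The strongest objection is that nothing here is wrong. A change-score comparison is valid under randomisation and agrees with the article's own power calculation. The ANOVA sentence formally concerns the time course, and the primary comparison has no model of its own. Covariate lists are commonly left to a full protocol or analysis plan, which is not shown. All of this stands, and it limits the point to efficiency. The point survives because the article does more than stay silent: it names one family of models and one outcome scale, and both are unadjusted change.

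Stronger readings are tempting but unsupported:

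- *The plan has decided to leave out baseline and strata.* The article says neither that it will adjust nor that it will not.
- *A known and sizeable amount of power is being lost.* ρ and the baseline SD are not given. The formula (1 + ρ)/2 also sits badly with the plan's figures: with a shared baseline SD, equal variances and one common ρ would give both arms the same change SD, not 16 and 6. Leaving out the cost of slope estimation would push the figures at ρ = 0.5, 0.7 and 0.8 up to 0.946, 0.918 and 0.903.
- *Chance baseline imbalance or regression to the mean biases the result.* Under randomisation these add variance, which the precision comparison already counts; they are not systematic bias.
- *The strata matter because they predict insulin level.* Differencing removes stable differences in level. In a change-score analysis they matter only if they predict the change, and nothing in the article shows that they do.

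**Conclusion.** The point holds as one of efficiency. The only between-group model named is, for group × day, an unadjusted change-score comparison without baseline as a covariate and without the two strata. It gives valid, unbiased estimates. In large samples it is never more precise than the baseline-adjusted comparison of two equal arms.

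The gain is uncertain. Under equal variances it runs from about 6 power points at ρ = 0.5 (0.936 against 0.873) through about 3 and 2 points at 0.7 and 0.8 to none at 0.9. With the plan's change SDs held fixed, the simulated scenarios run from about 2 points worse to about 2 points better. Any gain from the strata depends on an unknown share of variance. Adjustment is still worth specifying because the likely loss is small and the data are already collected.

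**What to change.** State a model for the primary exercise-versus-SUR comparisons: ANCOVA of follow-up insulin iAUC on arm, with baseline insulin iAUC, PAL stratum and body-mass stratum as covariates. Allow residual variances to differ by arm, since the planning SDs are 16 and 6. Report the three exercise-minus-SUR contrasts with 95% confidence intervals. Keep the group × day × time ANOVA for the time course, which is the use the article gives it.

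The cost is wording and three degrees of freedom (22 to 19 in a two-group comparison). If the covariates explain nothing beyond the change score, power falls slightly: from 0.873 to about 0.855 with baseline alone at a slope of 1, and to about 0.851 with both strata added. Allowing for unequal variances has its own cost (0.854 by Welch against 0.873 pooled, for the change score). The adjusted figures above assume a pooled variance, so power for the full recommended model should be computed once ρ and the baseline SD have been taken from the sponsor's previous study.

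### Magnitude-based inference is named for judging clinical significance without error control; under its usual rule, with 12 per arm, about 12% of null comparisons would be labelled as favouring exercise

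*Protocol article*

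**What the plan says.** The Statistical analysis section of the protocol article takes three steps.

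- It names the main contrast: "The statistical analysis plan is for a primary comparison between intervention groups and control arm". There are three exercise arms, so this means three comparisons with SUR.
- It adds two- and three-way mixed-model analyses of variance, then fixes the error level at p ≤ 0.05 in a sentence that opens: "For all the above statistical approaches, statistical significance will be set at an alpha level of".
- One further sentence closes the section: "We will explore the use of confidence intervals and magnitude-based inferences to assess the clinical significance of the effect".

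The Power calculation section sets the arm size: "a sample size of 12 in each treatment group will provide approximately 90% power". The effect behind that figure, in nmol 120 min L⁻¹, is given as "a difference in ∆ insulin iAUC of 17 ± 16 versus 1 ± 6". The calculation rests on a t test for two independent groups, with its error level worded as "at an alpha level of 0.05".

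The article gives no smallest worthwhile effect, no probability cut-offs and no choice between the clinical and non-clinical forms of magnitude-based inference.

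**The concern.** Magnitude-based inference turns the estimate and its standard error into chances that the true effect is substantially positive, trivial or substantially negative. Under its usual non-clinical rule, a result is called unclear only if both substantial directions have a chance above 5%. It is therefore enough to make a substantial effect in one direction unlikely. That is a one-sided 5% test against a shifted null, which is easier to pass than a test of no effect.

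The sentence stands after the 0.05 level has been tied to the approaches above it, so that level does not cover it. The objectives ask whether each of three forms of exercise can prevent metabolic deterioration. With 12 men per arm, some contrasts may well miss p ≤ 0.05. Such a contrast could still be reported as a likely substantial benefit, under a rule whose error rate the plan does not control.

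**Working it through.** **Inputs from the protocol article.** 12 per arm; difference 17 − 1 = 16; SDs 16 and 6; alpha 0.05, taken as two-sided; three comparisons with SUR.

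**Assumptions, because the article gives no figure.** The decision rule described above, counting labels of *possibly* (25%) or stronger; a smallest worthwhile effect of 0.2 SD, varied below; normal data.

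**1. The plan's own figure.**
- Root-mean-square SD = √[(16² + 6²)/2] = √146 = 12.08.
- Standard error of a difference = 12.08 × √(2/12) = 4.93.
- Normal approximation: 16/4.93 = 3.24, and 3.24 − 1.96 = 1.28, which gives power of 90.0%.

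The stated power is reproduced. The noncentral t gives 87.3%, which does not bear on this point.

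**2. Where the rule starts to call an effect clear.**
- Smallest worthwhile effect = 0.2 × 12.08 = 2.42 units, or 2.42/4.93 = 0.49 standard errors.
- The chance of a substantial effect in the opposite direction falls below 5% once |t| exceeds t(0.95; 22 df) − 0.49 = 1.717 − 0.490 = 1.227.
- With no true effect, P(|t| > 1.227) on 22 df = 0.233. Half of this, 0.116, lies in each direction.
- In units of insulin iAUC, an observed difference of 1.227 × 4.93 ≈ 6.1 earns a label. The two-sided 5% t test needs 2.074 × 4.93 ≈ 10.2.

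At this threshold, requiring *likely* (at least 75%) instead of *possibly* changes little: 23.2% with the threshold scaled by the sample SD, 21.9% by the true SD.

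**3. Simulation.** 200,000 null trials, 12 per arm, shared control, threshold 0.2 SD:

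| | Usual rule | t test at 0.05 |
|---|---|---|
| Label in either direction, per comparison | 23–24% | 5.0% |
| Label favouring exercise, per comparison | about 12% | 2.5% |
| Either direction, at least one of three arms | about 50% | 12.5% |
| Favouring exercise, at least one of three arms | about 25% | about 6% |

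The 23% scales the threshold by the sample SD and the 24% by the true SD. With the protocol's unequal SDs (16 and 6) and Welch standard errors, the either-direction rate is 22.5%.

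**4. Sensitivity to the threshold.** The favourable rate is half the either-direction rate, by symmetry.

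| Smallest worthwhile effect (SD) | 0.1 | 0.2 | 0.3 | 0.5 | 0.8 | 1.0 |
|---|---|---|---|---|---|---|
| Either direction, sample-SD scaling | 15.6% | 23.2% | 33.6% | 59.5% | 21.6% | 9.2% |
| Favouring exercise (half) | 7.8% | 11.6% | 16.8% | 29.8% | 10.8% | 4.6% |

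With true-SD scaling, the favourable rates at 0.1, 0.2, 0.3 and 0.5 SD are about 8, 12, 18 and 26%.

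**5. Sensitivity to the variant, at 0.2 SD.**
- Clinical rule relaxed by a benefit-to-harm odds ratio above 66: 11.3% called beneficial.
- Strict clinical rule (chance of benefit at least 25%, of harm below 0.5%): 1.7% called beneficial (1.5% with sample-SD scaling). The same rule calls 42.2% harmful.
- Unclear judged on a 99% interval: 3.0% in either direction. This rises to 12.5% at 0.5 SD.
- Only *very likely* labels counted: 3.8% in either direction.

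**The case against.** The best defence has three parts.

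First, the method is only to be explored. It comes after the p-value tests, beside confidence intervals, and addresses clinical rather than statistical significance. This stands: nothing in the article lets it overrule a p value, and the 0.05 level of the named tests is intact.

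Second, the threshold and cut-offs used above are assumptions, and a condensed article may leave such details to a fuller document. This also stands: their absence is not the complaint, and no single rate can be pinned on the trial. The complaint is that the article names a method whose usual rule is laxer than the plan's own alpha.

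Third, some variants are strict. A reader might infer that magnitude-based inference always labels null effects far more often than 5%. The documents do not support that, because no variant is chosen and several stay below 5% at 0.2 SD. They are not a general rescue, though: the strict clinical rule is strict for benefit only, and the 99% version loosens as the threshold grows.

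A reader might also take the 23–24% per comparison, or the 50% across three arms, as the rate of false claims for exercise. Those figures count labels in both directions. In the direction of a claim for exercise they are about 12% and 25%.

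**Conclusion.** The point holds in a limited form and is worth acting on. The article proposes a route to statements about clinical significance that lies outside its 0.05 level. Under the usual non-clinical rule, 12 per arm, no true effect and an assumed threshold of 0.2 SD, labels favouring exercise would appear in about 12% of comparisons, against 2.5% for the t test, and in at least one of three arms in about 25% of trials. Between 0.1 and 0.5 SD the favourable rate per comparison runs from about 8% to 26% (30% if the threshold is scaled by the sample SD). Strict variants can bring it below 5%, to 1.7% for benefit at 0.2 SD. The error rate is thus set by a choice that the article leaves open. It would be wrong to conclude that the trial's primary false-positive rate is inflated: the comparisons tested at p ≤ 0.05 are unaffected.

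**What to change.** In the last sentence of the Statistical analysis section, delete the words that add magnitude-based inferences and keep the confidence intervals already promised. Report a 95% interval for each of the three exercise-versus-SUR contrasts, and judge clinical relevance by where it lies relative to a smallest worthwhile difference in the change in insulin iAUC that the investigators state before analysis.

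The change affects only analysis and reporting, so it needs no new data and loses no information. The small cost is that the investigators must choose and justify that difference. The article does not supply one: the figures in the Power calculation section come from the previous study and are not offered as a smallest worthwhile effect. Whether the three intervals should be adjusted for multiplicity is a separate matter.
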